**Fig. 2 Fig2:**
[figure not shown]
Schedule of enrollment, interventions, and assessments, according to the SPIRIT 2013 statement

**Table 1 Tab1:** Time schedule for the in-hospital clinical trial

Day	Day 1				Day 2				Day 3			Day 4			
Time points	15:00	17:00	18:00	19:00	00:00	6:00	12:00	18:00	6:00	12:00	18:00	6:00	12:00	18:00	19:00
Time after exercise		–1 h	0 h	1 h	6 h	12 h	18 h	24 h	36 h	42 h	48 h	60 h	66 h	72 h	
Blood pressure		○		○		○		○	○		○	○		○	
Check for adverse events				○		○		○	○		○	○		○	
Physical examination	○														
Body composition analysis	◎														
IPAQ-SF questionnaire	◎														
Treadmill exercise			○												
Medication				○		○	○	○	○	○	○	○	○		
Randomization			○												
Blood tests		○												○	
Serum CK analysis		○				○		○			○	○		○	
Serum CRP, IL-6		○	○	○	○	○		○							
Pain intensity assessments		○	○	○	○	○		○	○		○	○		○	
Calf circumferences		○	○	○	○	○		○	○		○	○		○	
Pain threshold		○	○	○	○	○		○	○		○	○		○	
Serum & urine collection		○		○										○	
Blind assessment															○

◎ Assess only at the first hospitalization (Phase I)

*IPAQ-SF* International Physical Activity Questionnaire-Short Form, *CK* creatine kinase, *CRP* C-reactive protein, *IL-6* interleukin-6

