### Randomization and allocation concealment

Subjects will be randomly allocated to either the JGT or the placebo group with equal probability. An independent statistician will use SAS version 9.4 software (SAS Institute, Cary, NC, USA) to generate a random allocation list and will send the list to the pharmaceutical company for packing. The random allocation list will assign 30 subjects to group A or B. According to the crossover design, both groups will take JGT and the placebo drug. Subjects in group A will take JGT and those in group B will take the placebo drug during their first hospitalization.

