### Statistical analysis

The statistical analysis will be conducted by an independent statistician using SAS version 9.4 (SAS Institute). The significance level will be set at 0.05 in a two-tailed test. All continuous data will be presented as means and 95% confidence intervals (CIs). Categorical data will be reported as frequencies and percentages. The intention-to-treat (ITT) principle will be applied for the primary analysis. The ITT population will include subjects who meet the full analysis set (FAS) criteria, including subjects who had the primary outcomes assessed once or more except for the baseline measures and who took the test drug at least once. Subjects who do not meet the eligibility criteria, those who did not take the test drug throughout the study, and those who have never been evaluated after the screening visit will be excluded from the FAS dataset. The per-protocol set will also be analyzed, which will only include subjects who have completed the study as a supplementary analysis.

The baseline characteristics of the study subjects will be presented using a descriptive analysis for each group. The primary outcome will be the differences between the VAS score with motion measured at various intervals from 0 to 72 h after exercise. A mixed-effect model for repeated measures (MMRM) will be used to assess differences along with the time effect. The dependent variable will be the change in the VAS score (pain with motion) measured from 0 to 72 h after exercise. The model will include treatment and protocol-specified visits as fixed effects, and subjects as a random factor. Dunnett’s test will be used for multiple comparisons. The results of the secondary effective analysis will be analyzed using the same method as for the primary outcome, in the case of continuous variables with time variation. Additionally, Student’s *t* test or Wilcoxon’s signed-rank test will be used to compare results before and after the treatment within each group. Categorical data will be analyzed using the chi-squared test or Fisher’s exact test. Missing values by maximum likelihood will be considered when the MMRM is used. The last observation carried forward method will be adopted for missing values for Student’s paired *t* test, the Wilcoxon signed-rank test, or repeated measures analysis of variance.

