The incidence of serious adverse events (SAEs) and adverse events (AEs) related to the treatment will be analyzed for the safety assessment using the independent *t* test or Wilcoxon’s rank-sum test. The percentage of subjects who experienced one or more side effects during the study will be analyzed using Pearson’s chi-squared test or Fisher’s exact test.

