### Adverse events

During the hospitalization, subjects will be asked if they have any physical discomfort other than DOMS symptoms. Occurrence of any AEs will be recorded on the eCRF after assessing severity and causality. If a SAE occurs, it will be reported to the IRB as soon as possible. If suspected unexpected serious adverse reactions occur, they will also be reported to the Ministry of Food and Drug Safety according to the relevant regulations.

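### The side-effect percentage is not tied to the drug taken: read literally it merges JGT and placebo, and read by drug its tests ignore the pairing

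*Protocol article*

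**What the plan says.** The last paragraph of the Statistical analysis section has two safety analyses. The first reads "The incidence of serious adverse events (SAEs) and adverse events (AEs) related to the treatment will be analyzed for the safety assessment using" an independent t test or rank-sum test. The second, at issue here, reads "The percentage of subjects who experienced one or more side effects during the study will be analyzed using" Pearson's chi-squared or Fisher's exact test. The second sentence fixes a unit (the subject), an event (at least one side effect), a window (the study) and a pair of tests. It does not name the groups compared, and it does not say by drug, by stay or by period.

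The design is a 2 × 2 crossover. Under Randomization and allocation concealment: "According to the crossover design, both groups will take JGT and the placebo drug". The same section defines the sequences: "Subjects in group A will take JGT and those in group B will take the placebo drug during their first hospitalization". Study design adds that the whole process is repeated with the other drug after the wash-out.

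On data collection, the Table 1 row "Check for adverse events" is marked at 1, 12, 24, 36, 48, 60 and 72 h of a stay. The Adverse events section says that men are asked about discomfort while in hospital, and that "Occurrence of any AEs will be recorded on the eCRF after assessing severity and causality".

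**The concern.** For every man who completes the trial, the study contains one JGT stay and one placebo stay. A yes/no taken over the whole study therefore pools the two drugs. Chi-squared and Fisher tests need disjoint groups, and with one value per man the only randomized disjoint groups are sequences A and B. Comparing them sets JGT-then-placebo against placebo-then-JGT, which is not a drug contrast. A non-significant result would be almost guaranteed by construction, and it could be reported as JGT being no worse than placebo.

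If the sentence is instead meant as a count by drug, the two percentages come from the same men, and the named tests do not fit paired data. The sentence needs changing on either reading, but the consequences differ greatly.

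**Working it through.** **Inputs from the protocol article.** There are 30 men: "The random allocation list will assign 30 subjects to group A or B". An even split gives 15 per sequence. The level is given by "The significance level will be set at 0.05 in a two-tailed test". The article states no event rate, power or sample size for safety, so there is no figure of its own to reproduce.

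**Assumptions.** Event rates p_J (JGT) and p_P (placebo), and the correlation between a man's two stays.

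**Step 1: literal reading, sequence A v B.** For a man with both stays,

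P(any event) = p_J + p_P − P(event in both stays).

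Apart from order effects this does not depend on which drug came first, so it is equal in A and B for any p_J and any correlation. With independent stays it is 1 − (1 − p_J)(1 − p_P). At 40% and 10% this is 1 − 0.60 × 0.90 = 0.46, or 15 × 0.46 = 6.9 expected men with an event in each sequence. The null hypothesis of the A v B test is true whatever JGT does.

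**Step 2: by-drug reading.** The same rates give 30 × 0.40 = 12 men with an event on JGT and 30 × 0.10 = 3 on placebo.

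Exact binomial enumeration of the rejection rates at two-sided 0.05 (chi-squared uncorrected, stays independent):

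| Placebo v JGT | P(any), either sequence | A v B, 15 v 15: chi-squared | A v B: Fisher | By drug, 30 v 30: chi-squared | By drug: Fisher |
|---|---|---|---|---|---|
| 5% v 25% | 28.8% | 0.055 | 0.017 | 0.63 | 0.44 |
| 10% v 40% | 46% | 0.046 | 0.016 | 0.80 | 0.71 |
| 10% v 60% | 64% | 0.051 | 0.016 | 0.99 | 0.99 |
| 5% v 80% | 81% | 0.048 | 0.016 | 1.00 | 1.00 |

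Down the table the A v B columns stay at the level of the test, while the by-drug columns climb to 1.

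**Step 3: cost of ignoring the pairing.** With n = 30 pairs, the variance of the difference in percentages is [p_J(1 − p_J) + p_P(1 − p_P) − 2 cov]/n. Chi-squared and Fisher leave out the covariance, so positive correlation makes them conservative. Simulation (20,000 runs per scenario, latent correlation 0 / 0.3 / 0.6):

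| | Chi-squared | Fisher | Exact McNemar |
|---|---|---|---|
| Type I error, 20% on both drugs | 0.050 / 0.033 / 0.015 | 0.022 / 0.012 / 0.004 | 0.021 / 0.018 / 0.013 |
| Power, 10% v 40% | 0.80 / 0.82 / 0.84 | 0.70 / 0.73 / 0.74 | 0.68 / 0.76 / 0.84 |

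Exact McNemar is itself conservative, because its distribution is discrete. At 10% v 40% it does better than Fisher at correlations of 0.3 and 0.6, and it only draws level with uncorrected chi-squared at 0.6. So on the by-drug reading the loss from the named tests is modest. The large loss belongs to the literal reading.

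**The case against.** The strongest reply is that nobody intends to compare sequences. The safety paragraph names no groups, and no section says that A and B are compared on any outcome. Objective and Metabolomics analysis both use JGT and placebo groups to mean the drug. On that usage *during the study* is loose wording for a by-drug count, and harm is then detectable with the very tests named. This stands: the by-drug reading is as fair as the literal one.

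A reader might go further than the text allows and infer that side effects in this trial cannot be assigned to a drug, or that the plan cannot detect harm from JGT. The documents do not support either. Events are checked seven times per stay, each stay uses one drug, and causality is recorded, so the data can be split by drug. The trial also has a separate analysis of treatment-related event incidence, and blood tests before and after the drug in each hospitalization.

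It can also be said that attribution windows belong in the full protocol or analysis plan, which are not shown. That would answer a complaint about a missing detail. Here the article states a window and a class of test, and together they do not fit its own crossover on either reading. Nor does the by-drug reading clear the sentence, since it still treats 30 men as 60.

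**Conclusion.** The point holds as a defect of specification. As worded, the analysis either merges the two drugs or treats paired data as independent.

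- **Literal reading:** no power beyond the level of the test. At 40% v 10% the rejection rates are 1.6% (Fisher) and 4.6% (chi-squared). That there is no drug contrast does not depend on the assumed rates. It requires only that order effects are absent and that men complete both stays.
- **By-drug reading:** harm is detectable, with power of about 0.80 (chi-squared) and 0.71 (Fisher) at the same rates. The fault is then conservatism under positive correlation: type I error of about 0.015 and 0.004 at latent correlation 0.6 and true rates of 20%.

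The article does not settle which reading is meant, so it would be wrong to assert that its safety test is blind to harm. It should be amended because one fair reading gives a test that cannot inform on JGT, and its null result could be taken as reassurance. All event rates and correlations are assumptions.

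**What to change.** Replace the whole-study window with a count per drug. For each hospitalization, count the men with at least one event with onset after the first dose of that stay and up to its last scheduled adverse-event check at 72 h, and tabulate by drug taken. Compare the two percentages within subject, by exact McNemar or by a period-adjusted test such as Mainland-Gart. Report the whole-study percentage only as description.

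At 40% v 10%, exact McNemar has power of about 0.68 to 0.84 for latent correlations from 0 to 0.6. The window stops at 72 h because adverse events are described as collected only during hospitalization, so a window running through the wash-out would need data that the article does not describe.

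The cost is one sentence. The checks already scheduled in each stay supply the data. The change should be made before unblinding, or else be reported as a later change.

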### Data management and monitoring strategies

All source documents, including informed consent forms, questionnaires, and worksheets, will be collected in compliance with standard operating procedures. The data will be collected on an electronic data capture system through electronic case report forms (eCRFs) using the Medidata RAVE data management system (Medidata Solutions Inc., New York, NY, USA). The Korea Institute of Oriental Medicine will be responsible for quality control throughout the study. An independent clinical research associate will regularly monitor the overall process to determine if the trial is performed in accordance with the protocol.

### Adverse events

During the hospitalization, subjects will be asked if they have any physical discomfort other than DOMS symptoms. Occurrence of any AEs will be recorded on the eCRF after assessing severity and causality. If a SAE occurs, it will be reported to the IRB as soon as possible. If suspected unexpected serious adverse reactions occur, they will also be reported to the Ministry of Food and Drug Safety according to the relevant regulations.

## Discussion

This is a protocol for a randomized, double-blind, placebo-controlled, crossover-designed clinical trial to study the efficacy and safety of the herbal medicine JGT in the relief of DOMS in healthy male adults. The strength of this study lies in the rigorous design. In general, DOMS is difficult to test in a clinical trial because of the short duration of the symptoms. A standardized method for pain induction and a rigorously designed clinical trial will provide reliable results on the therapeutic effects of JGT in DOMS. The Standard Protocol Items: Recommendations for Interventional Trials (SPIRIT) checklist is attached as Additional file 1. This study will provide a better understanding of the mechanisms of JGT for relieving muscle pain in general, as DOMS is an important experimental model to evaluate analgesic efficacy and to study movement-related pain [40, 41]. We expect to provide novel insights into potential biological mechanisms of JGT through a metabolomics approach. In this protocol, the inclusion criteria of the study participants will be narrowed to male adults, and participants will be hospitalized during the intervention. Therefore, the results of the metabolomics analysis are expected to yield reliable results, because factors affecting metabolites, such as age, gender, and food intake, will be controlled [42, 43]. Moreover, as this is a 2 × 2 crossover design study, each subject will serve as his own control to reduce individual variations.

To our knowledge, no clinical trial has evaluated the therapeutic effects of JGT on exercise-induced muscle pain. Several clinical trials have evaluated the antispasmodic and analgesic effects of JGT. Clinical trials of JGT to reduce pain have mostly considered pain caused by complications, such as muscular cramps of patients on hemodialysis and myalgia caused by chemotherapy [44–48]. Although it is widely prescribed to manage muscle soreness and myalgia, it is difficult to find any evidence other than a clinical study about JGT on painful muscle cramps in patients with lumbar spinal stenosis [49]. A retrospective case series study with 37 patients treated with JGT for muscle spasms and pain was published in 2004 [16]. However, the current clinical trial will be the first to assess the effect of JGT on exercise-induced muscle soreness. This study will provide valuable data to determine the clinical effects of JGT on exercise-induced pain.

### Trial status

This study was approved by the Pusan National University Korean Medicine Hospital IRB (IRB approval number 2018013). The most recent version of the protocol is version 1.4 (3 January 2019), and this was also approved by the IRB. Recruitment began on 7 February 2019. This study is expected to be completed by August 2019.

## Data Availability

The final dataset of the clinical trial will be accessible to all authors and the Ministry of Food and Drug Safety (MFDS).

## Abbreviations

AE: Adverse event
CK: Creatine kinase
CRP: C-reactive protein
DOMS: Delayed-onset muscle soreness
eCRF: Electronic case report form
FAS: Full analysis set
IL-6: Interleukin-6
IPAQ-SF: International Physical Activity Questionnaire-Short Form
IRB: Institutional review board
ITT: Intention-to-treat
JGT: Jakyakgamcho-tang
MET: Metabolic equivalent
MMRM: Mixed-effect model for repeated measures
NRS: Numeric rating scale
PID: Pain intensity difference
SAE: Serious adverse event
SPID: Sum of pain intensity differences
VAS: Visual analog scale
